### Sample size

#### *Triangle taste test*

Given that three coded food samples will be presented to each participant, two similar and one odd, there is a probability of 33% of randomly selecting the appropriate sample. However, if a participant can differentiate between the two types of samples, since two are similar, the actual probability is 50%. Assuming a significance level of 5% and a power of 90%, approximately 146 participants will be required, as described previously elsewhere [25].

##### 

**Formative research** For this component, approximately 228 participants are needed to have enough opinions in the focus groups (n = 168) and in-depth interviews (n = 60). Focus groups will include healthy and hypertensive participants from different villages stratified by sex and age (20 to 44 and 45 to 65 years old). Separately, in-depth interviews will be conducted among hypertensive individuals as well as community or local stakeholders. We expect to enroll approximately 10 participants from each village for the interviews. Of these, 5 will be individuals with hypertension, whereas the other 5 will be stakeholders, e.g., community health leaders and authorities, commercial traders, health workers, and others.

#### *Stepped wedge trial*

Calculations were derived using preliminary data from the baseline of the CRONICAS cohort study in Tumbes [28] and the PERU MIGRANT study estimates [29]. Power for the stepped wedge design was computed for a continuous endpoint [30], where X is a *N x T* matrix showing the treatment pattern, i.e., X_ij_ = 1 if cluster ‘i’ received the intervention at time ‘j’ and 0 otherwise. We assumed a significance level of 5%, a standard deviation of blood pressure within sites of 20 mmHg (σ), the number of clusters (N) as 6, the number of time periods (T) as 6 (excluding baseline assessment), the average number of subjects assessed per cluster and time period as 300, and τ, an approximation to the coefficient of variation, as 0.20. Based on those assumptions, we calculated a power over 90% to find a difference (θ) of 3 mmHg in blood pressure levels between the intervention and control groups. This magnitude of difference is within the expected range that provides major public health gains in the long-term, in particular in reduction of stroke [8]. Typically, the coefficient of variation ranges between 0.15 and 0.40, but when this value is unknown, as in this study, sensitivity of the sample size within this range needs to be verified [31]. In this protocol, power calculations using both extremes of coefficient of variation yields a power greater than 90%.

### Statistical analysis

#### *Triangle taste test*

We will be able to determine whether the total number of correct responses for the total number of participants is statistically significant based on the critical number of correct responses in a triangle taste test. Thus, there is a one out of three chance that the correct (odd) sample will be picked just by chance (guessing). We will then compute a z-statistic based on the following formula:

$$z=\frac{\left(k-\left(n/3\right)\right)}{\sqrt{2n/9}}$$

In this formula, ‘n’ is the total number of subjects assessed and ‘k’ is the number of correct responses [32]. Based on these results, we will reject the hypothesis of ‘no difference’ between samples if the number of correct responses is significantly greater than the calculated value (z).

##### 

**Qualitative data** Information from focus group sessions and in-depth interviews will be recorded and transcribed. All the collected information will be segmented, entered, coded, and analyzed using Atlas.Ti to identify a list of relevant themes and thus, identify key concepts to create our social marketing campaign. Coding will be carried out using the grounded theory approach to data analysis, where the data emerges from the participants, not the researchers [33,34]. The analysis will compare the information obtained from different subgroups of participants in order to identify and describe the similarities and divergences between men and women, patients from different age groups, and health workers and stakeholders. The analysis will also include notes from the field, i.e., fieldwork diary and minutes of the researchers’ meetings.

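### Read literally, the triangle taste test's rejection sentence compares the count of correct answers with its own z statistic, so it rejects 'no difference' for every result

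*Protocol article*

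**What the plan says.** Protocol article, Statistical analysis, Triangle taste test. The paragraph opens by saying that significance will be judged "based on the critical number of correct responses in a triangle taste test". It gives the chance probability: "there is a one out of three chance that the correct (odd) sample will be picked just by chance (guessing"). It then defines z = (k - n/3)/sqrt(2n/9), where n is the number of subjects assessed and k "is the number of correct responses [32"]. It closes with the decision: 'no difference' is rejected "if the number of correct responses is significantly greater than the calculated value (z"). Neither a critical value for z nor a critical count appears.

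Protocol article, Sample size, Triangle taste test. The alternative is set by "since two are similar, the actual probability is 50" per cent, and the size by "Assuming a significance level of 5% and a power of 90%, approximately 146 participants will be required". The text does not say whether the 5% is one-sided or two-sided, or whether 146 applies to each comparison or to all three together.

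Protocol article, Phase 1: Exploratory phase. Common salt is to be compared with samples containing 25%, 33% and 50% potassium chloride, to assess whether their taste is acceptable.

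**The concern.** The statistic z measures how far k lies from its chance expectation n/3, in standard deviations. It has to be judged against a normal critical value. Alternatively, k can be judged against a critical count. The closing sentence does neither: it compares k with z, two quantities on different scales, one calculated from the other.

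This is a stated rule that is wrong as worded, not a detail left to a fuller document. It also disagrees with the opening of its own paragraph, so a reader cannot tell from the article which rule was applied. A rule that always rejects could not separate the three concentrations from one another or from common salt, which is the purpose of the test.

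**Working it through.** **Inputs.** Chance probability 1/3 and z = (k - n/3)/sqrt(2n/9), from Statistical analysis. Alternative 0.50, significance level 5%, power 90% and n of about 146, from Sample size.

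**The plan's own figure.** The one-sample formula, one-sided, gives n = (1.645 x sqrt(2/9) + 1.282 x sqrt(1/4))^2 / (1/2 - 1/3)^2 = 72.2, so 73. Two-sided it gives 88.1, so 89. The stated 146 is not reproduced, although it equals 2 x 73. That is a separate matter. It is used here only as the planned n, and the result below does not depend on it.

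**The statistic.** Under guessing, k has mean n/3 and variance n x (1/3) x (2/3) = 2n/9. The formula for z is correct.

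**The literal rule, k > z.** Write s = sqrt(2n/9). Then

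k - z = k(1 - 1/s) + n/(3s).

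For n of 5 or more, s is above 1, so the first term is never negative and the second is positive. Hence k > z for every possible k. The gap is smallest at k = 0, where it equals n/(3s) = sqrt(n/2).

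| n | smallest gap k - z | results with k > z |
|---|---|---|
| 146 | sqrt(73) = 8.54 | all 147 |
| 49 | sqrt(24.5) = 4.95 | all 50 |

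At n = 146, z runs from -8.54 (k = 0) to 17.09 (k = 146). Reading 'significantly greater' as a margin of 1.645 or 1.96 changes nothing, because the gap is never that small. The literal rule therefore has a false rejection probability of 1, against the stated 5%.

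**A conventional rule at n = 146.** Here n/3 = 48.67 and s = 5.696.

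- One-sided, z > 1.645: k must exceed 48.67 + 1.645 x 5.696 = 58.04, so k of at least 59. The exact binomial tail at 59 is 0.0437, and at 58 it is 0.0619. The exact rule gives the same count.
- Two-sided, z > 1.96: k must exceed 59.83, so k of at least 60. The exact upper tail is 0.0300, slightly above 0.025; the exact binomial count is 61 (tail 0.0202).

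**If 146 were split over three comparisons** (an assumption: 146/3 = 48.7, about 49 each). With n = 49, n/3 = 16.33 and s = 3.300. The exact one-sided count is 23 (tail 0.0331). The normal approximation would already reject at 22 (z = 1.717), where the exact tail is 0.0610. The two forms of the rule can therefore differ by one answer, and the text should name the one that governs.

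**The case against.** The strongest reply is that this is a slip of wording. The same short paragraph names a critical number of correct responses, gives the right chance probability and the right statistic, and cites a method source. The sample size section sets a 5% level. Nobody would compute z only to reject with zero correct answers. Read as a whole, the paragraph points to the conventional test. This stands, and it limits the consequence. It does not repair the sentence, because no critical number is given and the closing rule puts z in its place.

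Two stronger readings are tempting, and the documents do not support them.

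- A reader might infer that Phase 1 was analysed with a 100% false positive rate. That figure describes only the literal sentence. Nothing shows that anyone intended or applied it.
- A reader might infer that the wrong substitute could have gone into Phase 2. The article says that the test assesses acceptability of taste and that Phase 1 feeds the social marketing campaign. It does not say that rejecting 'no difference' decides among 25%, 33% and 50%. The link is plausible, but it is an inference.

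It is also fair to object to a fixed count of 59. That count assumes 146 assessments in each comparison and a one-sided 5% level, and the article states neither. With about 49 per comparison, 59 would exceed the number tested.

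**Conclusion.** The point holds as a wrongly worded decision rule. For any n of 5 or more, the closing sentence rejects 'no difference' whatever the data, contrary to the 5% level and to the critical number named in the same paragraph. This follows from the formula alone and does not depend on 146, on sidedness, or on how participants are divided among concentrations. Those matter only for the replacement critical count.

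The consequence is limited. A drafting error is the likely explanation, and the stepped wedge power calculation and blood pressure analysis make no use of this test. What remains open is whether the completed Phase 1 result used a valid rule, which the article does not show.

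**What to change.** Replace the closing sentence with wording such as: 'For each concentration, reject no difference if z exceeds the critical value for the 5% significance level (1.645 if one-sided), or if k is at or above the exact binomial critical count for the number of assessments in that comparison.' Name one of the two as decisive, since they can differ by one answer.

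State whether the 5% is one-sided or two-sided, and give n for each comparison. As examples of the exact one-sided count: 59 if n = 146 per comparison, 23 if n = 49.

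The Trial status section says Phase 1 is complete, so the authors should also confirm that its reported result used this rule. The cost is one corrected sentence, two added facts, and a check of k and n for each concentration against the critical count. No new data are needed.

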#### *Stepped wedge trial design*

Descriptive and exploratory statistics using tabulations and graphical methods will be derived. This process will allow us to verify the data entry process as well to detect atypical values. Following careful checking, we will describe variables of interest, especially our numeric outcome, using appropriate central tendency measures (mean, median, etc.) and dispersion measures (standard deviation, inter-quartile range, etc.). Appropriate longitudinal and panel data analysis techniques will be used for the assessment of blood pressure levels from baseline to the end of the study. Since cluster sizes may vary, an efficient analysis at the cluster mean level requires weights that depend on unknown parameters. Thus, an analysis at the individual level using generalized estimating equations (GEE) or generalized linear mixed models are preferable. Of these, GEE can flexibly handle normal or non-normal endpoints and tends to be more robust to misspecification of the variance structure since ‘sandwich’ type variance estimates are used [35]. In the same sense, GEE uses within-cluster and between-cluster information to estimate the treatment effect. This approach is necessary to avoid confounding the treatment effect with changes over time [36].

##### 

**Economic evaluation** Cost effectiveness analysis can be used as a tool for measuring costs and health gains of interventions, which in turn can help in decision-making and resource allocation. At the first stage, we will develop a cost analysis associated with the patient costs and the program implementation. Patient costs involve costs of illness data for treating high blood pressure or its complications, i.e., cardiovascular drugs, medical visits, hospitalization, laboratory tests, special diets, physical therapies, blood pressure caregiving, and monitors and other devices needed. Program costs will include marketing campaign, training, administration, production, and delivery of the salt substitute, among other activities. Our effect indicators will be measured by different health outcomes: blood pressure level (mmHg), number of cases averted (CVDs and stroke), and disability-adjusted life years averted. An incremental cost effectiveness ratio will show us the additional cost of a unit of health gained. Our cost-effectiveness analysis methodology will follow the guidelines established by WHO-CHOICE [37] and recommendations given by the Disease Control Priorities Project [38].

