### Participant recruitment and selection criteria

Participants from six randomly-selected villages will be involved in the different phases of the study. Potentially eligible subjects will be identified from the most updated census available. Males or females aged 18 years and over from the randomly selected villages, capable of understanding study procedures, capable of providing informed consent, and full-time residents in the area are eligible. Only those participants with mental illness that impair their consent will be excluded. In the case of the stepped wedge trial, self-reported history of chronic kidney disease and heart disease will be considered as additional exclusion criteria.

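### GEE is preferred for sandwich-variance robustness, which needs many clusters; with six villages and no small-sample correction, a 5% test would run at about 17–23%

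*Protocol article*

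**What the plan says.** The Stepped wedge trial design part of the Statistical analysis section rejects a cluster-mean analysis because village sizes may differ. It names two individual-level options, GEE and generalized linear mixed models, and then argues for the first: "GEE can flexibly handle normal or non-normal endpoints and tends to be more robust to misspecification of the variance structure". The reason given is its sandwich-type variance estimates. The text names no primary model, working correlation, small-sample correction or reference distribution.

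The number of independent units is fixed elsewhere. Participant recruitment and selection criteria says "Participants from six randomly-selected villages will be involved in the different phases of the study". Table 2 has one village starting at each of six steps. The sample size section takes "the number of clusters (N) as 6", a 5% significance level, and "the average number of subjects assessed per cluster and time period as 300".

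**The concern.** The sandwich variance protects against a wrong working covariance only as the number of independent clusters grows. Here the village is both the randomised unit and the independent unit. Measuring 6 × 300 = 1,800 people per period does not add clusters. With six villages, the residuals that feed the sandwich have been shrunk by the fit, so the variance is biased low. It is also estimated from only six contributions, so it is unstable, and a normal reference allows for neither problem.

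The article therefore prefers one method for a property that the method does not have in this design. At stake are the p-value and interval for the effect on blood pressure, which is the trial's main quantitative aim. The same estimate also feeds the cost per mmHg in the economic evaluation.

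**Working it through.** **Inputs from the article.** Six villages, the Table 2 pattern, 300 people per village-period, within-village SD 20 mmHg, level 5% (taken as two-sided, which is not stated), and a target difference of 3 mmHg. Table 2 shows seven periods while the power calculation uses six without baseline, so both were run. Between-village variation is given as "τ, an approximation to the coefficient of variation, as 0.20". Its scale is unclear, so a range was used.

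**1. The stated power.** The closed-form stepped wedge variance with a village random intercept and fixed period effects is

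Var(θ̂) = Iσc²(σc² + Tτ²) / {(IU − W)σc² + (U² + ITU − TW − IV)τ²}

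Here σc² = 20²/300 = 1.333 and I = 6. U = 21 is the number of treated cells. W = 91 and V = 91 are the sums of squared column and row totals.

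- T = 7, τ = 0.2 mmHg: 6 × 1.333 × (1.333 + 7 × 0.04) = 12.91. The denominator is 35 × 1.333 + 140 × 0.04 = 52.27. Var = 0.247, SE = 0.497, and power = Φ(3/0.497 − 1.96), above 99.9%.
- T = 7, large τ: Var = 6 × 1.333 × 7/140 = 0.400, SE = 0.632, power 99.7%.
- T = 6, large τ: Var = 6 × 1.333 × 6/105 = 0.457, SE = 0.676, power 99.3%.

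The claim of over 90% reproduces on any reading of τ. It assumes, however, that the variance is known and the test is normal. It says nothing about whether the sandwich recovers that variance.

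**2. The sandwich under a true null.** With A = Σ Zᵢ′V⁻¹Zᵢ, the variance is A⁻¹{Σ Zᵢ′V⁻¹eᵢeᵢ′V⁻¹Zᵢ}A⁻¹, a sum of six village terms. On Table 2 there are 6 × 7 = 42 village-period means and 8 mean parameters (7 periods and treatment).

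The simulation used 4,000 replicates per scenario (Monte Carlo error about 0.6 points), equal village sizes and normal effects. Village SD was assumed to be 0.2, 2 or 4 mmHg and village-by-period SD 0, 1 or 2 mmHg.

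| Variance and reference | Two-sided type I error at nominal 5% |
|---|---|
| Uncorrected, normal, exchangeable | 16.7–19.8% |
| Uncorrected, normal, independence | 19.5–23.2% |
| Uncorrected, t(5) | 8.6–13.3% |
| Uncorrected, t(4) | 7.0–11.0% |
| Kauermann-Carroll, t(4) | 3.4–6.2% |
| Mancl-DeRouen, normal | 5.9–8.7% |
| Mancl-DeRouen, t(4) | 1.7–3.3% |

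On the seven-period layout alone, the uncorrected normal test gives 17.7–21.7%. The range hardly moves with village SD, so the unclear τ does not matter here.

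**3. Further runs on Table 2.** These gave 17–20% for the uncorrected sandwich with a normal reference and 7–9% with t(4). About 9–10% of null trials rejected in the beneficial direction, against a nominal 2.5%. The mean SE was 75–78% of the true SE. With unequal village sizes (assumed 100 to 550), a run of 2,000 replicates gave 18.8–24.6%.

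**4. Why the rate is so high.** An SE at 75–78% of its true value turns the 1.96 threshold into an effective 1.47–1.53. That alone gives a two-sided error of about 13–14%. The rest comes from the instability of a variance built on six terms.

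**5. Permutation test.** There are 6! = 720 village orders, so a 5% test is attainable (0.05 × 720 = 36 orders). It held 4.5–5.2% type I error. Power for 3 mmHg was about 92–99% at village-by-period SD 0–1 mmHg and about 63–81% at 2 mmHg.

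**The case against.** The strongest reply is that the article does not commit to the faulty procedure. The 17–23% needs GEE to be chosen, the sandwich to be uncorrected and the reference to be normal, and none of these is written down. Small-sample corrections and degrees of freedom are commonly left to a statistical analysis plan, which is not shown. This stands as a limit on the figure. It does not remove the point, because the fault lies in the reason the article gives for its preference, and that reason fails with six clusters. Adding only a t reference does not rescue it.

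The mixed model also remains permitted. In one run, a model-based analysis with the variance structure correct and assumed known held 5–6%. That is fair, and the headline rate does not apply to the mixed model. The text nevertheless argues away from it.

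Two stronger readings are tempting. A reader might take the mention of panel data techniques to allow clustering GEE on participants, ignoring village correlation. The same paragraph speaks of cluster sizes, cluster means and within- and between-cluster information, and clusters are villages throughout, so the document does not support this. A reader might also infer that 17–23% of null trials would declare the salt substitute effective. That figure is two-sided; the beneficial direction accounts for about 9–10%.

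**Conclusion.** The concern holds in conditional form. The stated ground for preferring GEE is a many-cluster property that six villages do not provide. Under the usual default, the two-sided error would be about 3.4 to 4.6 times the nominal level (17/5 to 23/5), and nominal 95% intervals would cover about 77–83% of the time. With a t reference alone, the error stays at about 7–13%.

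These rates rest on assumed village and village-by-period SDs and, in the main runs, on equal village sizes and normal effects. They do not show that the trial will be analysed this way, nor that the stated power is wrong on its own assumptions.

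**What to change.** - Remove sandwich robustness as the reason for preferring GEE.
- Take the primary p-value from a permutation test over the 720 village orders, and the confidence interval by inverting that test. Apply it to the treatment estimate from an individual-level model with fixed period effects and village-level clustering. The mixed model that the section already allows would serve, with random village, village-by-period and participant effects.
- If GEE is kept, cluster on village and use a small-sample-corrected sandwich with a t reference on about 4 df. Kauermann-Carroll is the better calibrated choice (3.4–6.2%). Mancl-DeRouen with t(4) is conservative at about 2%. In one run with village SD 3 mmHg, its power for 3 mmHg was 87%, 63% and 31% at village-by-period SD 0, 1 and 2 mmHg.
- Do not report the uncorrected sandwich with a normal reference as the primary result.

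The change needs wording and a short program, with no change to design, sample or data collection. The real cost is wider intervals and lower power. The plan should say that permutation power falls to about 63–81% if village-by-period SD reaches 2 mmHg, a quantity for which the article gives no value.

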### Ethical issues

This project was reviewed and approved by Institutional Review Boards at Universidad Peruana Cayetano Heredia (Peru) and Johns Hopkins University (USA). Informed consent for participation will be obtained from all human subjects prior to subject participation and confidentiality of subjects will be protected.

All study participants will be linked to a unique identification code. Data will be recorded both in paper form and electronically. The electronic information will be stored, backed up, and secured by password protection. Paper forms will be stored in secure locked cabinets. All personal information, including participant’s names, addresses, and dates of birth, will be stored in a file and password protected as well. Only study investigators will have access to confidential information.

